**Fig 3 pone.0287004.g003:**
[figure not shown]
Description of implementation of intervention. Involvement of the hospital administration in interevention phase before enrolling the post CS mothers and nurse midwives to the study.

**Variables definition and measurement. Independent variables:** In this study, the independent variables are socio-demographic characteristics of participants such as age, marital status, education level, past obstetric history, type of operation and economic factors for the post-CS mothers as well as the as age, sex, education level and duration of experience for nurse midwives.

### Intermediate independent variables

#### Hb level

Hb level will be measured using HemoCue Hb 201+ Haemoglobin photometer, which uses a capillary to collect blood after a figure prick. Participants will be classified as non-anaemic (≥ 11g/dl), mild (9.5–10.9g/dl), moderate (8–9.4g/dl), severe (6.5–7.9g/dl) or life-threatening (< 6.5g/dl) anaemia according to standard WHO criteria [45].

#### Reported home care practice

This care regimen is received by mothers at home after hospital discharge as per the post-CS home care guide. Mothers who report performing/receiving 75% of home care practice as per the guide will be regarded as having good practices, otherwise poor practice [47].

#### Dependent variables. Knowledge of post-CS home care

Participants who will score at least 75% of the maximum score will be regarded as possessing adequate knowledge of home care after CS, otherwise inadequate knowledge [47].

#### SSI

This involves inflammation and positive bacterial culture from the wound within 30 days after CS [48]. It can be associated with redness, pain around the wound area, foul odour, and any discharge from the wound [49, 50]. The diagnosis and classification of SSI wound infection will be based on CDC criteria within 30 days [48] at the interval of 7^th^, 14^th^ and 30^th^ days after CS during post-natal clinic visits. A Blueberry Wound Healing Questionnaire (WHQ) will be used to assess signs and symptoms of SSI [49]. The tool comprises signs and symptoms for a ‘not at all’ (score 0), ‘a little’ (1), ‘quite a bit’ (2) and ‘a lot’ (3), where the higher score will suggest an SSI. Further, in order to minimise observation bias, two research assistants will assess the wounds. The confirmation is made through microbiological culture and isolation of microbes which aid in the management of the wound.

#### Analysis

In this study, data will be analysed by using the Statistical Product for Service Solutions (SPSS) software program version 25.0. Before conducting the analysis, data will be cleaned using frequency distribution tables to ensure the accuracy of data entry. Continuous data will be treated for normality to determine the measure of analysis (parametric and non-parametric analysis).

### Analysis of demographic data

Descriptive analysis will establish frequencies and percentages of socio-demographic characteristics profiles of the study participants and will be presented in tables and figures in order to establish distribution proportions between groups.

The Chi-square test will be used to analyse the categorical data and to establish the relationship between the categorical variables and the outcome variables that are post-intervention knowledge on home care after CS and SSI.

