**Fig 1 pone.0287004.g001:**
[figure not shown]
Conceptual framework guiding the study, developed from self-care deficit theory and consolidated framework for implementing research. The interaction of independent and depend varibles; Both the nurses, environment (both home and hospital environment), human that is post caesarean section mothers and the designed intervention are the independent variables that define the dependent variables that are knowledge on home cre acre Surgical Site Infection (SSI).

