#### Study population

The study will include registered nurse midwives and post-CS mothers. In addition, post-caesarean mothers in post-natal wards will be retained to participate in the study before discharge. The exclusion criteria will be:

Post-CS mothers with prolonged hospitalisation due to maternal or neonatal complications.Post-CS mothers who didn’t receive pre-antibiotic medication prior to surgery, have an infection of amniotic fluid.Mothers whose CS were not performed in the study site (DRRH and SRRH).

Post-CS mothers in the intervention group will be matched based on their age, gravidity, type of CS and their obstetric history such as the previous mode of delivery. Also, nurse midwives will be matched based on their education level and working experience in a maternity unit.

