#### Sampling and method

A purposive sampling method will be used to select DRRH and SRRH [42]. SRRH and DRRH are both regional hospitals, have specific blocks for maternity care, and offer CEmONC. The intervention has been assigned by hospital settings where DRRH will be selected to be an intervention site because of its higher prevalence of SSI (48%) to post-CS mothers [19], and SRRH will serve as a control site.

Nurse-midwives and post-CS mothers will be selected by using a simple random sampling method [40]. Specifically, lottery replacement methods will be employed where the replacement selection of participants will be done to ensure an equal chance of selection to all until the desired sample size is achieved [40].

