### Analysis of knowledge of home care after CS

The outcome variable is dichotomised (1 = adequate knowledge; 0 = inadequate knowledge), and so a generalised estimating equation (GEE) will be employed to assess the impact of the intervention on knowledge, whereby odds ratio, confidence interval and p-value will be presented. GEE is an extension of the ordinary logistic regression model for correlated/repeated measure data. In this case, it seems to be more appropriate as will be having more than one measurement/observation of each subject at different time points.

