### Analysis of SSI

Binary logistic regression analysis will be used to assess factors associated with SSI.

The general logistic regression model is given as:

$$\log it[\pi (x)]=\log(\frac{\pi (x)}{1-\pi (x)})=\beta_{0}+\beta_{1}x_{1}+\ldots \ldots +\beta_{p}x_{p}$$

Where *π*(*x*) is the SSI status, *x*_*i*_’*s* is set of independent variables and *β*_*i*_’*s* is their respective parameters.

The power of the study will be set at 80% (0.8) while a confidence interval of 95% with a margin of error of 5% (0.05) was used as a statistical measure of significance (< 0.05 was regarded as significant while > 0.05 not significant).

The effect of intervention between groups will be assessed using difference in difference (DID) analysis.

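### The chi-square factor tests for SSI and post-intervention knowledge are not stratified by hospital, so a characteristic that merely differs between the two hospitals can look like a factor.

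*Protocol article*

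**What the plan says.** All references are to the Protocol article, Phase 4.

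- **Analysis of demographic data.** The chi-square test is to be used "to establish the relationship between the categorical variables and the outcome variables that are post-intervention knowledge on home care after CS and SSI". Nothing is said about doing this within hospital or within arm.
- **Analysis of SSI.** "Binary logistic regression analysis will be used to assess factors associated with SSI". The model is written out in general form, and its covariates are not listed.
- **Variables definition and measurement (after Fig 3).** For mothers, "the independent variables are socio-demographic characteristics of participants such as age, marital status, education level, past obstetric history, type of operation and economic factors". Arm and hospital are not in the list, which is introduced as a set of examples.
- **Fig 1 caption.** Nurses, the home and hospital environment, the mothers and "the designed intervention are the independent variables that define the dependent variables".
- **Sampling and method.** "The intervention has been assigned by hospital settings", with Dodoma Regional Referral Hospital as the intervention site and Singida Regional Referral Hospital as the control site. Arm and hospital are therefore the same variable.
- **Study population.** "Post-CS mothers in the intervention group will be matched based on their age, gravidity, type of CS and their obstetric history". Nurse midwives are matched on education and maternity experience.
- **Intervention effect.** This is handled elsewhere. For knowledge, "a generalised estimating equation (GEE) will be employed to assess the impact of the intervention on knowledge". Under Analysis of SSI, "The effect of intervention between groups will be assessed using difference in difference (DID) analysis".

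**The concern.** The question behind a factor test is whether, among comparable women, a characteristic goes with the outcome. A two-way table of all mothers asks something else: whether the two are associated in a 1:2 mixture of one taught and one untaught hospital. If the outcome rate differs between the hospitals, for any reason, a characteristic whose frequency also differs becomes associated with the outcome in the combined table, even with no relation inside either hospital. A two-way chi-square has no place for a hospital term that would remove this.

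At stake is how any reported list of factors is read. Some entries could be stand-ins for the hospital where the woman delivered, and a reader could take them as risk factors for SSI or as determinants of knowledge. The logistic model could correct this if it contains arm, but the text does not settle whether it does.

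**Working it through.** **Inputs from the protocol (Sample estimation).**
- The formula as printed, with the plan's values: 2 × (1.96 × √(0.16 × 0.84) + 0.8 × √(0.049 × 0.951)) / 0.111² = 144.7, so 145. Then 145 × 1.05 = 152.25, so 152 intervention mothers; 2 × 152 = 304 controls; total 456. The plan's figures are reproduced and serve here only as group sizes.
- SSI 16% and 4.9%. The plan defines these as before and after proportions in the intervention group.
- Significance level 5%, two-sided.

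**Assumptions.**
- The protocol gives no SSI rate for the control hospital. I use 4.9% (intervention) v 16% (control) as an illustrative contrast.
- It gives no prevalence of any characteristic by hospital. I take a binary characteristic with prevalence q₁ in the intervention hospital and q₂ in the control hospital, unrelated to SSI inside each.

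**Step 1: expected combined table.**
SSI rate with the characteristic: P₁ = (152·q₁·0.049 + 304·q₂·0.16) / (152·q₁ + 304·q₂). Without it: the same expression with 1 − q₁ and 1 − q₂, giving P₀.

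For 40 v 60%:
- P₁ = (2.979 + 29.184) / 243.2 = 0.1323
- P₀ = (4.469 + 19.456) / 212.8 = 0.1124
- Odds ratio = (0.1323/0.8677) / (0.1124/0.8876) = 1.20, where the true value inside each hospital is 1.

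For 30 v 70%: P₁ = 36.282/258.4 = 0.1404, P₀ = 19.806/197.6 = 0.1002, odds ratio 1.47.

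**Step 2: approximate false-positive rate.**
Overall SSI rate = (7.448 + 48.64)/456 = 0.123. Standard error of P₁ − P₀ = √(0.123 × 0.877 × (1/N₁ + 1/N₀)), where N₁ and N₀ are the numbers with and without the characteristic. With z = (P₁ − P₀)/SE, the rejection rate is P(Z > 1.96 − z) + P(Z < −1.96 − z).
- 45 v 55%: z = 0.321; 0.051 + 0.011 = 6.2%
- 40 v 60%: z = 0.643; 0.094 + 0.005 = 9.9% (9.85% before rounding)
- 30 v 70%: z = 1.295; 0.253 + 0.001 = 25.4% (25.35% before rounding)

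**Step 3: simulation (20,000 runs per row, 152 v 304 mothers).**

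| Prevalence, intervention v control | Odds ratio, combined table | Unstratified chi-square rejects | Cochran-Mantel-Haenszel by hospital rejects |
|---|---|---|---|
| 50 v 50% | 1.00 | 5.2% | 5.1% |
| 45 v 55% | 1.10 | 6.2% | 5.0% |
| 40 v 60% | 1.20 | 9.9% | 5.0% |
| 30 v 70% | 1.47 | 24.9% | 5.0% |
| 20 v 80% | 1.84 | 51.3% | 4.7% |

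Simulation and approximation agree. With equal prevalence there is no inflation, which identifies the between-hospital difference as the cause.

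**Step 4: knowledge.**
The plan's 63.4% and 44.8% come from a before/after study of nurses. Borrowed as a between-hospital contrast for mothers (152 v 304), they give unstratified rejection rates of 6.4%, 11.1% and 30.1% at 45 v 55%, 40 v 60% and 30 v 70%. For nurses (82 v 164) the rates are 8.1% at 40 v 60% and 18.0% at 30 v 70%. Stratified tests stay at 4.9 to 5.1%.

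**The case against.** The strongest reply has five parts.

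1. **The logistic model may well contain arm.** A reader might infer from the list of independent variables that arm is left out. The document does not support that. The list is illustrative; later sections add haemoglobin and reported home care practice, the Discussion adds labour and operation factors, and the Fig 1 caption counts the intervention among the independent variables. A complete covariate list may also sit in an analysis plan that is not shown. This stands: the text is unsettled, and omission is not shown.
2. **The intervention effect is analysed elsewhere.** A reader might conclude that the guide's effect on SSI or knowledge is distorted. GEE and difference in difference are assigned to it, so this point does not reach those estimates. The factor tests serve no listed objective and are secondary. This stands.
3. **The SSI contrast is borrowed.** The 16% and 4.9% are before/after figures, not rates for two hospitals. It is also tempting to say that a more effective guide creates more spurious factors. That need not hold for SSI: the intervention hospital was chosen for a reported SSI prevalence of 48%, so if it starts above the control hospital, a working guide would first narrow the gap. This stands.
4. **The imbalance is assumed, and matching limits it.** For mothers, matching should restrain age, gravidity, type of CS and obstetric history. For nurses it covers education and experience, leaving age and sex. This stands in part, because education, marital status and economic factors are unmatched for mothers.
5. **Pooling is implied, and bivariate tests can be read as descriptive.** The stated purpose, however, is to establish a relationship with the outcomes. A chi-square described without strata would ordinarily be run on everyone together.

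**Conclusion.** The point holds as a secondary analysis flaw. As written, the chi-square tests do not separate the association of a characteristic with the outcome from the difference between two hospitals that are also the two arms. Under the assumed SSI contrast of 4.9% v 16%, the false-positive rate for SSI is about 6% for a slight imbalance (45 v 55%), 10% at 40 v 60% and 25% at 30 v 70%, against about 5% when stratified. Both the contrast and the imbalances are assumptions. If the hospitals have similar outcome rates or a similar mix of women, the inflation is small or absent. Spurious factors are thus a risk and not a certainty.

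On the logistic model, the conclusion is only that the Fig 1 caption, the variable definitions and the Analysis of SSI section leave the presence of an arm term undecided.

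**What to change.** - **Analysis of demographic data:** test characteristics against post-intervention knowledge and SSI stratified by hospital (Cochran-Mantel-Haenszel). Equally acceptable: treat the bivariate tests as descriptive and take factor conclusions only from a model that includes arm.
- **Variables definition and Analysis of SSI:** name arm (hospital) as a mandatory term in the SSI logistic model, so that the other odds ratios are within-hospital. Label the arm odds ratio as a between-hospital comparison, since arm and hospital cannot be separated.
- **Keep** the plain chi-square for comparing characteristics between arms.

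This is a change of wording and needs no new data. The cost is slightly less precision for characteristics strongly tied to hospital, and some apparent factors may no longer reach significance.

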### Analysis of knowledge of home care after CS

The outcome variable is dichotomised (1 = adequate knowledge; 0 = inadequate knowledge), and so a generalised estimating equation (GEE) will be employed to assess the impact of the intervention on knowledge, whereby odds ratio, confidence interval and p-value will be presented. GEE is an extension of the ordinary logistic regression model for correlated/repeated measure data. In this case, it seems to be more appropriate as will be having more than one measurement/observation of each subject at different time points.

### Analysis of SSI

Binary logistic regression analysis will be used to assess factors associated with SSI.

The general logistic regression model is given as:

$$\log it[\pi (x)]=\log(\frac{\pi (x)}{1-\pi (x)})=\beta_{0}+\beta_{1}x_{1}+\ldots \ldots +\beta_{p}x_{p}$$

Where *π*(*x*) is the SSI status, *x*_*i*_’*s* is set of independent variables and *β*_*i*_’*s* is their respective parameters.

The power of the study will be set at 80% (0.8) while a confidence interval of 95% with a margin of error of 5% (0.05) was used as a statistical measure of significance (< 0.05 was regarded as significant while > 0.05 not significant).

The effect of intervention between groups will be assessed using difference in difference (DID) analysis.

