### Methodology

#### Study design

Quasi-experimental study design with the non-equivalent control group (pre-and post-test with a control group) will be conducted [42]. The design will involve a baseline assessment of knowledge of post-CS and nurse midwives on home care after hospital discharge both in the intervention and control groups [42]. The intervention group will be exposed to a post-CS home care guide and education for both post-CS mothers and nurse midwives, respectively. In contrast, the nurse midwives and post-CS mothers in the control group will not be exposed to the post-CS home care guide and education but they will receive the usual care offered in their facility.

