*Assessment and education of post-caesarean mothers*. Before the intervention, the pre-tested tool will be used by the researcher and RA to assess baseline knowledge of post-CS mothers on home care after CS. Both the assessment and intervention of post-CS mothers will be done before discharge. The education intervention about home care will be given in one group depending on the number of post-CS discharged on that day. The intervention will involve slides projection of the post-CS home care and distribution of leaflets with simplified Swahili language and pictures demonstrating recommended home practices after CS. This will be followed by the questions and answers session for more clarification. The intervention will take about 1 hour including a question-and-answer session. This will be performed every day before discharge until the sample size is met. The researcher and other RA (nurse midwives in the profession) will be providing this education to post-CS mothers to ensure the home care guide after CS is delivered effectively. Thereafter, the participants will be instructed to come for the usual recommended post-natal visits to the same facilities for follow-ups that is, on the 7^th^, 14^th^ and 30^th^ day. On the 7^th^ day post-delivery, mothers will be instructed to come for stitch removal, assessment of the wound and other routine post-natal check-up services. In all visits, the post-CS mothers will be requested to report their practices at home, and assess their haemoglobin level to establish their anaemia status using the WHO classification [45]. For the purpose of this study, mothers will be instructed to come down to the facility on the 30^th^ day post-CS to evaluate their prognosis, to assess wound healing and their recovery in general. The wound assessments will be performed by two researchers and research assistants to minimise observer bias. For all wounds with SSI, their samples will be taken for culture to confirm the diagnosis. On the same day (30^th^-day post-delivery), a post-interventional assessment of the knowledge of post-CS home care will be done [46], after being exposed to the home environment.

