*Assessment and training of nurse midwives*. The intervention by nurse-midwives will be followed after the intervention of the post-CS woman. They will also be trained in a written post-caesarean home care guide and its use the guide to educate post-natal mothers. Before the training, the pre-tested tool will be used to assess the baseline knowledge of nurses on post-CS home care. Thereafter, nurse midwives will be trained on the component and content of the guide and how they would use the guide to educate post-CS mothers. The intervention will be done in the hospital environment (meeting room) to ensure maximum participation of the study participants. The session will involve lecturing and lecturing discussion. The intervention will involve two training sessions scheduled on two different days since it is difficult to get all of the nurse-midwives in one day. The intervention will take three hours including the time for pre-interventional assessment. Thereafter, they will be post-tested on the same day. After the intervention, nurse midwives working in the post-natal ward will be required to provide home care education intervention to post-CS mothers, for making this intervention sustainable.

At SRRH, the control group of nurse midwives and post-CS mothers will not be exposed to the content of the developed home care guide. Nurse midwives will continue to provide their usual care to post-CS mothers at the facility. The control group will also be assessed for baseline knowledge of home care after CS. Post-CS mothers will be assessed first, they will be assessed for baseline knowledge about home care after hospital discharge before discharge, as in the interventional group.

Knowledge of participants on home care after CS and SSI status will be compared between the intervention and control group. To ensure equal treatment of both groups, nurse midwives in the control group will be trained on the post-CS home care guide and how to deliver the content to post-CS mothers after meeting the sample size of post-CS, where they will also be required to train post-CS mothers to ensure the sustainability of the intervention. The implementation of the intervention has been described in the Fig 3.

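### Difference-in-difference is named for the SSI effect, but no pre-intervention SSI is measured, so only an adjusted post-only comparison of two hospitals can be estimated

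*Protocol article*

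**What the plan says.** Analysis of SSI gives binary logistic regression for factors associated with SSI and then adds: "The effect of intervention between groups will be assessed using difference in difference (DID) analysis". The sentence names no outcome. Knowledge has its own analysis section, with a GEE model.

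On what is measured before the intervention, the Phase 4 Study design section says: "The design will involve a baseline assessment of knowledge of post-CS and nurse midwives on home care after hospital discharge". The Intervention section says of Singida: "The control group will also be assessed for baseline knowledge of home care after CS". Neither mentions SSI.

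On timing, the Intervention section says: "Both the assessment and intervention of post-CS mothers will be done before discharge". The definition of SSI begins "This involves inflammation and positive bacterial culture from the wound within 30 days after CS", and SSI is assessed "at the interval of 7^th^, 14^th^ and 30^th^ days after CS during post-natal clinic visits".

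On the sites, Sampling and method says: "DRRH will be selected to be an intervention site because of its higher prevalence of SSI (48%) to post-CS mothers". SRRH is the single control site, and no SSI rate is given for it. Study population plans matching of mothers on age, gravidity, type of CS and obstetric history. The Discussion plans to use labour, operation and medical-history data in the inclusion criteria and in the model.

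**The concern.** A difference-in-difference estimate is built from four quantities: the outcome rate before and after, in each group. The protocol provides two of them for SSI. The named estimator and the measurement schedule are therefore incompatible. A fuller analysis plan could not repair this, because it cannot analyse pre-period data that the design does not collect.

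Preventing SSI is the aim in the abstract, a study objective and a Phase 4 objective, and the Discussion foresees possible adoption by the Ministry of Health. If the analysis falls back on comparing the two hospitals after the intervention, any underlying difference in SSI between them enters the estimate in full. Such a difference is plausible, because DRRH was selected on its SSI rate. A useful guide could look ineffective, or an ineffective one useful.

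**Working it through.** **1. The plan's own figure.** Sample estimation uses 16% and 4.9%. Its printed formula, taken literally, gives 2{1.96√(0.16×0.84) + 0.8√(0.049×0.951)} / 0.111² = 144.67, or 145. With 5% attrition this is 152, with 304 controls and 456 in total. The figure reproduces. It sizes one contrast of two proportions, not a four-cell difference-in-difference.

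**2. Is there a pre-intervention SSI value?** Baseline assessment is of knowledge only, in both hospitals. Mothers are educated before discharge, and the first SSI visit is day 7. No earlier SSI cohort or record audit is described. The 16% labelled as baseline is a literature input to the sample size. Using each mother's own pre-education state does not help: wound SSI is essentially absent then in both groups, so the estimate collapses to the post-only difference.

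**3. What the post-only contrast estimates.**

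Post-only difference = true effect + (underlying DRRH rate − underlying SRRH rate).

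Assumptions: the guide works at the planned ratio, 4.9/16 = 0.31. DRRH's untreated rate is either 48% (Sampling and method) or 16% (Sample estimation). SRRH's rate is assumed at values within the 11% to 48% that the Introduction gives for Tanzania. Odds ratio = [p/(1−p)] / [c/(1−c)], where p is the treated DRRH rate and c the SRRH rate.

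| DRRH untreated → treated | SRRH (assumed) | Post-only odds ratio |
|---|---|---|
| 48% → 14.7% | 11% | 0.1723/0.1236 = 1.39 |
| 48% → 14.7% | 16% | 0.1723/0.1905 = 0.90 |
| 48% → 14.7% | 48% | 0.1723/0.9231 = 0.19 |
| 16% → 4.9% | 11% | 0.0515/0.1236 = 0.42 |
| 16% → 4.9% | 16% | 0.0515/0.1905 = 0.27 |

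The relative risk reduction is the same in every row. Only the underlying hospital rates differ.

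**4. No effect at all, 145 v 290 mothers, two-sided 5%.** With underlying rates of 16% (DRRH) and 11% (SRRH), the pooled rate is (145×0.16 + 290×0.11)/435 = 0.1267. The null SE is √{0.1267×0.8733×(1/145 + 1/290)} = 0.0338, and the unpooled SE is √(0.1344/145 + 0.0979/290) = 0.0356. P(significant harm) = Φ{(0.05 − 1.96×0.0338)/0.0356} = Φ(−0.46), about 32%. With the rates reversed, significant benefit appears in about 28%.

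**5. Precision if a pre-period were added** (DRRH 16% → 4.9%, SRRH constant at 16%):
- 300 baseline records per hospital: SE = √(2×0.1344/300 + 0.0466/145 + 0.1344/290) = 0.041. Then 0.111/0.041 = 2.71, and power is about 77%.
- Baseline cohorts of 145 and 290: SE = √(0.1344/145 + 0.0466/145 + 2×0.1344/290) = 0.0466. Then 0.111/0.0466 = 2.38, and power is about 66%.

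**The case against.** The strongest reply is that the sentence names no outcome, and that the method is feasible for knowledge, which is measured at baseline and on day 30 in mothers. That is fair, and part of the repair may be a single sentence. But the sentence stands under Analysis of SSI, and knowledge has its own section and model. If it was meant for knowledge, the SSI section offers only a regression for associated factors and no stated estimator of the guide's effect. The text needs correction on either reading.

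A second reply is that confounding is addressed. Mothers are to be matched, mothers without pre-operative antibiotics or with amniotic fluid infection are excluded, and labour, operative and medical factors enter the model. A reader might infer that the comparison is wholly unadjusted, and the documents do not support that. These measures work on measured patient characteristics, however. With one hospital per arm, hospital and intervention are the same variable, and no patient covariate separates them.

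A third reply is that the non-equivalent, two-hospital design is openly declared. That stands: the design is a disclosed limitation. The fault is in naming an estimator that the design cannot supply.

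A fourth is that apparent harm needs DRRH at 48% and SRRH at 11%, the two ends of the range. That also stands. From the plan's own 16%, the contrast points to harm only if SRRH is below 4.9%, outside the range.

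**Conclusion.** The point holds as a contradiction between estimator and data: as designed, a difference-in-difference for SSI cannot be estimated, and the remaining comparison cannot distinguish the guide from the hospital. The size of the bias is unknown because SRRH's rate is not given. Under the assumed rates, the odds ratio for one and the same relative effect runs from 0.19 to 1.39. The 48% and 16% figures, which the text attaches to the same hospital, are not reconciled, so even the starting point is uncertain.

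Three stronger readings are tempting and should not be drawn:

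- **The guide will look harmful.** The direction of the bias depends on SRRH's rate, and the 16% scenarios do not show harm.
- **A fall at DRRH would be regression to the mean.** The study observes no fall, because it has no pre-period. The argument would apply only if a historical rate were used as the before value, which the protocol does not propose.
- **The p-values fail because mothers are treated as independent.** Any patient-level analysis of these two hospitals, including the alternatives below, makes the same assumption, so it is not an argument for this change.

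**What to change.** 1. Restrict the difference-in-difference sentence to knowledge.
2. For SSI, name as the main analysis a logistic model with a term for group, the matching variables, and the pre-operative and operative confounders that the protocol already plans to take from patient files and history. State that the result is an adjusted difference in SSI between two hospitals and does not by itself show effectiveness of the guide. Reconcile the 48% and 16% figures for DRRH.
3. Only if pre-launch SSI can be obtained at both hospitals with a comparable definition and follow-up, replace item 2 by a logistic model with hospital, period and their interaction, and take the interaction as the intervention effect.

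Items 1 and 2 change wording only. Their price is a weaker SSI claim than the objectives now promise.

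Item 3 needs data collection at both sites and is conditional. The prospective outcome is assessed at three visits with culture confirmation, and the documents do not show that past records hold this. Differences in record quality between hospitals could bias the estimate. Precision falls to the powers of about 77% and 66% worked out above. The estimate would still rely on parallel trends and on independence of mothers within two hospitals.
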